### Participant outcomes

#### Primary outcomes

***Detection and documentation of NAFLD in people with T2D.*** A diagnosis of NAFLD will be made following a participant’s FibroScan with a CAP score ≥ 248 dB, with documentation in a letter to the patient’s GP and Diabetes Specialist.***Detection and documentation of significant liver fibrosis in people with T2D.*** This will be calculated based on the number of participants who receive a diagnosis of significant fibrosis (LSM ≥8.0 kPa), with documentation in a letter to the patient’s GP and Diabetes Specialist.

#### Secondary outcomes

***Rate of referral of “high-risk” NAFLD to Hepatology***. This will be calculated based on the number of “high-risk” patients referred to Hepatology clinics.***Rate of referral of “low-risk” NAFLD to Hepatology.*** This will be calculated based on the number of participants who receive a diagnosis of NAFLD without clinically significant fibrosis (LSM < 8.0 kPa), and the number of these “low-risk” patients that are referred to Hepatology clinics.***Rate of surveillance for HCC among “high-risk” patients.*** This will be calculated based on the number of participants with cirrhosis who are referred for surveillance for HCC according to guidelines (with liver imaging, usually ultrasound, every 6 months).***Collection of evidence about the economic benefits of a NAFLD detection/risk stratification pathway in people with T2D.*** Costs associated with the new pathway will be collected by the research team using published costing methods. Modelling will permit estimation of an incremental cost per appropriate referral via the pathway versus usual care that can be considered in light of undesirable consequences, including those associated with delayed detection and referral. Diagnostic performance of the pathway in identifying cases of advanced fibrosis will be compared with usual care.***Longitudinal outcome data.*** Participant outcome data will be collected at 12 months, 5 years and 10 years post recruitment. Linkage to Hospital Admitted Patient Data, Emergency Department data, Cancer Registry, and Death Registration will be performed by the Queensland Health Data Linkage Team for all participants. Data items will include: 1) details about hospital admissions and emergency presentations: dates, primary/other diagnosis, procedures and use of hospital-based allied health services and hospital-based clinical costings; 2) cancer (any type): date of diagnosis, site, morphology, differentiation, basis of diagnosis; 3) date and cause of death.***Development of procedures and referral pathways to facilitate patient access to required services.*** The study clinician will develop resources for the service (GP template letters). Knowledge and attitudes of clinic/community clinicians will be surveyed post-implementation of the pathway (at 2 years).***Collection of usual care data.*** Usual care data will be collected retrospectively from the three study sites for the year prior to recruitment commencement. Eligibility and exclusion criteria of controls will be the same as the intervention group except for patient consent (we will seek a waiver of consent to collect available data from patient medical records). The data collected for this usual care group will include demographic information, anthropometric measurements (height, weight, BMI, waist circumference), relevant metabolic co-morbidities, diabetes medications, and whether there is a record of alcohol consumption, a diagnosis of NAFLD and management of NAFLD – including risk stratification, blood tests, simple fibrosis scores, radiological investigations and/or referral to liver clinics.

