### Hypotheses

Compared with patients receiving usual care, people with T2D using the NAFLD pathway are hypothesized to benefit in the following ways:

H1: increased identification of NAFLD.

H2: increased identification of people at increased risk of advanced fibrosis/cirrhosis.

H3: increased referral of people with ‘high-risk’ NAFLD to Hepatology clinics and reduced referrals of ‘low-risk’ NAFLD to Hepatology clinics.

H4: increased surveillance for HCC among people with a diagnosis of cirrhosis.

H5: resource use and net-costs of the new pathway for NAFLD diagnosis and risk stratification in the community will be sustainable relative to existing usual care.

H6: GP knowledge and confidence in the recognition, diagnosis, risk stratification and management of NAFLD in their practice population will improve.

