### Design and setting

This clinical trial examines the implementation of a diagnostic and risk stratification pathway for NAFLD in people with T2D. Sequential participants will be recruited to the NAFLD-RRR pathway and followed for up to 10 years to monitor their health outcomes. The detection of patients with NAFLD ± advanced fibrosis and the surveillance for HCC among “high-risk” patients will be compared to patients receiving “usual care”.

Due to the high prevalence of NAFLD and advanced fibrosis in people with T2D, it is not appropriate to conduct a randomized study of screening and risk stratification versus no intervention. All people attending the community diabetes clinics will be offered participation in the study. Study outcomes will be compared to a cohort who received “usual care” at the community diabetes clinics in the 12-months prior to implementation of the NAFLD-RRR pathway. The medical records of “usual care” patients will be audited to determine the number of people with a recorded diagnosis of NAFLD, whether an assessment of liver disease severity was performed, and the number of people referred to a liver clinic.

The study will be conducted in 3 “Beacon” diabetes clinics in the Metro South hospital and health services district (HHS), where people who are referred by their GP for specialist management of T2D are offered specialised care in a primary care setting. The Beacon model for people with complex T2D is delivered through community-based general practices where GPs with a special interest (GPwSIs) and advanced training in diabetes work alongside an endocrinologist and diabetes nurse educator [28]. The model is an alternative to standard hospital outpatient review and is fully integrated, with primary care providers and specialists co-located to provide effective, cost-efficient and patient-centred care [29]. In this model the GPwSIs take their enhanced skills back to their routine practice, so they become a referral point and source of knowledge for colleagues, potentially reducing referrals to specialist clinics. Prior to developing and implementing the NAFLD-RRR pathway, diabetes clinic/community clinicians (*n* = 24) were invited to participate in focus group discussions to obtain information about preferences and strategies for learning, support and communication [30].

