#### Other clinical information

At the FibroScan assessment the study clinician will assess girth and document alcohol consumption using the short form AUDIT [37] to quantify alcohol misuse, based on 3 questions posed to patients about their consumption habits. A short medical history form (Table 1) will be completed to obtain information about the following: prior diagnosis, management and follow-up of fatty liver; prior hepatology review; year of diagnosis of T2D; presence of other cardiometabolic risk factors (obesity, hypertension, dyslipidaemia); presence of cardio- cerebro- or peripheral vascular disease, history of cancer; mental health; family history of fatty liver; medications; current employment status (full-time, part-time, unemployed, disability pension); sociodemographic data (e.g. marital status, education level, country of birth, place of residence).

**Table 1 Tab1:** Clinical data collected at NAFLD-RRR appointment

Demographic information	
Age	
Ethnicity	
Language spoken at home	
Country of birth	
Sex	
Menopausal status – pre, peri, post	
Relationship status – single, married or de factor, divorced/separated, widowed	
Level of education – junior, senior high school, TAFE, university	
Employment status – full time, part time, unemployed, disability pension	
Medical history	
Year T2D diagnosed	
Cardiometabolic risk factors – obesity, hypertension, dyslipidaemia,	
Metabolic comorbidities – cardiovascular disease, atrial fibrillation, cerebro- and/or peripheral vascular disease, obstructive sleep apnoea, chronic kidney disease, gout	
History of malignancy – primary cancer type and year diagnosed	
Patient-reported NAFLD	
Previous diagnosis of NAFLD	
Year NAFLD diagnosed	
Investigations for NAFLD diagnosis	
Previous hepatology review	
Current Medications	
Lifestyle	
Smoking status – yes/no/previous and pack-years	
Alcohol consumption	
Physical activity	
Depression Inventory	
Family history of liver disease	
Fatty liver disease	
Liver disease	
Cirrhosis	
Liver cancer	

The patient will be diagnosed with NAFLD on the basis of the FibroScan CAP score (CAP score ≥ 248 dB considered as likely steatosis based on cut-offs determined in a large meta-analysis) [38] and stratified to low or high risk of clinically significant fibrosis on the basis of the FibroScan liver stiffness measurement (LSM).

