No NAFLD: Participants with CAP score < 248 dB and LSM < 8 kPa will be classified as “no NAFLD”. A letter will be sent to the patient’s GP and diabetes specialist advising a repeat FibroScan or liver ultrasound in 3–5 years if appropriate, to screen for development of NAFLD. Participants will be informed of their FibroScan result at the NAFLD-RRR appointment and advised to follow up with their GP.

NAFLD with low risk of clinically significant fibrosis: Participants with CAP score ≥ 248 dB and low FibroScan score (LSM < 8.0 kPa) will be classified as ‘Low Risk’. A letter will be sent to the patient’s GP and diabetes specialist advising a repeat FibroScan in 2–3 years if appropriate, to assess for development of clinically significant fibrosis. If liver enzymes are abnormal, the letter to the participant’s GP will include guidance for further evaluation of abnormal liver enzymes.

High risk of clinically significant fibrosis: Participants with LSM ≥8.0 kPa will be classified as ‘High Risk’. The study clinician will advise the patient (and GP and diabetes specialist via letter) that Hepatology referral is recommended. A letter will be sent to the patient’s GP advising them to arrange a Hepatology Clinic referral. To assist GPs with this process, referral guidelines will be included with the patient’s letter and FibroScan result. If advanced fibrosis is confirmed in the secondary care hepatology clinic, the patient may be offered ongoing hepatology follow-up that may involve HCC and variceal surveillance programs.

For all patients with NAFLD, the letter to the GP and diabetes specialist will provide recommendations regarding management of NAFLD with ongoing assessment and management of cardiometabolic risk factors and lifestyle intervention with consideration of referral to a dietician, exercise physiologist and psychologist for assistance with weight management and increased physical activity. Patients diagnosed with NAFLD at the study clinic visit will receive a patient letter at the conclusion of the clinic visit. This letter advises patients to make an appointment to see their GP to further discuss the recommendations advised by the study team. The template letters are provided in Supplementary Figs. 1-4.

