This study does have limitations. The sole use of FibroScan for a diagnosis of advanced chronic liver disease is likely to overestimate the prevalence of advanced disease owing to its modest positive predictive value of 59% for advanced fibrosis [23]. However the diagnostic gold standard of liver biopsy carries an unjustifiable risk of adverse outcomes if implemented as a screening tool. FibroScan is a well validated NIT that can simultaneously assess hepatic steatosis and the risk of advanced fibrosis as a “point-of-care” test. It has one of the highest negative predictive values (84%) of all NITs currently available for clinical use in Australia to exclude advanced fibrosis/cirrhosis in people with type 2 diabetes [23]. Although the positive predictive value is lower at 59%, the reporting of outcome measures in this population will reduce the clinical significance of this overestimation [23]. Whilst allowing a rapid assessment for NAFLD, FibroScan requires a dedicated operator and is not currently widely available in the community. ShearWave elastography, available in many community radiology centres, has similar accuracy to FibroScan for the exclusion of advanced fibrosis although the test is not as well validated as FibroScan [48, 49].

Our study will provide important information about the feasibility of establishing a NAFLD pathway for people with T2D in primary care and the costs and health outcomes associated with the pathway compared to those experienced under usual care. The study represents a change to the current management model for chronic liver disease, in which people seek care to treat complications of progressive fibrosis, rather than maintaining health through illness prevention. As recently reported by the President of the American Academy of Family Physicians “ … we need to invest in a new model that would allow primary care clinicians and their teams to coordinate care locally, collaborate with community organizations and public health departments, maximize strengths of specialists, and address known social drivers of health … ” [50, 51].

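### The risk-split referral comparison with usual care (H3) rests on study FibroScan classes that the audited controls largely lack, and the planned test of overall referral does not replace it

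*Protocol article*

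**What the plan says.** **The hypothesis is comparative.** Protocol article, Hypotheses: compared with usual care, H3 expects "increased referral of people with ‘high-risk’ NAFLD to Hepatology clinics and reduced referrals of ‘low-risk’ NAFLD to Hepatology clinics".

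**Both classes come from the study scan.** Other clinical information: "Participants with LSM ≥8.0 kPa will be classified as ‘High Risk" and "Participants with CAP score ≥ 248 dB and low FibroScan score (LSM < 8.0 kPa) will be classified as ‘Low Risk". Secondary outcomes builds the low-risk referral rate on "participants who receive a diagnosis of NAFLD without clinically significant fibrosis (LSM < 8.0 kPa". The same section plans an economic outcome, the added cost of each appropriate referral relative to usual care, which needs the same classes in both arms.

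**The comparator is a chart audit.** Design and setting says usual-care records will be checked for a NAFLD diagnosis, "whether an assessment of liver disease severity was performed, and the number of people referred to a liver clinic". Secondary outcomes lists the control items on NAFLD management as "risk stratification, blood tests, simple fibrosis scores, radiological investigations and/or referral to liver clinics". Neither place names liver stiffness (LSM) or the steatosis score (CAP), and neither maps an audited patient to low or high risk. The Discussion adds that "FibroScan requires a dedicated operator and is not currently widely available in the community".

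**The planned test has no risk split.** Data analysis compares the proportion referred to Hepatology before and after implementation, as a single proportion for Aim 3.

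**Primary outcomes.** In the pathway, "The patient will be diagnosed with NAFLD on the basis of the FibroScan CAP score", and fibrosis rests on LSM. In usual care, the audit looks for a recorded diagnosis.

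**The concern.** The article fixes three things that do not fit together: a comparison by risk class, a class definition that needs a study scan, and a comparator without study scans. Following the text literally, an analyst has no denominator for either control referral rate, except for controls who happen to have an LSM on file.

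Those controls are unlikely to be a fair sample. If FibroScan is scarce in the community, an LSM on file was probably often obtained because the patient had been referred. A referral rate among such patients is biased upwards in both classes. H3 would then look better than it should on low-risk referral and worse than it should on high-risk referral.

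At stake are the article's claim about reducing unnecessary referrals and the economic result that depends on it.

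**Working it through.** **1. The plan's own figure.** Sample size and statistical power gives 400 patients, about 60% with NAFLD (n = 240), 20% of these with advanced fibrosis, and a 95% interval of 15.4 to 25.5%. The Wilson interval with p = 0.20, n = 240, z = 1.96 is

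(p + z²/2n ± z·√[p(1−p)/n + z²/4n²]) / (1 + z²/n) = (0.2080 ± 0.0512) / 1.0160 = 15.43% to 25.52%.

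This reproduces. The arithmetic is sound, but it describes the pathway group only.

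**2. Pathway denominators.** 400 × 0.60 = 240 with NAFLD; 240 × 0.20 = 48 high-risk; 240 − 48 = 192 low-risk. This treats the plan's 20% with advanced fibrosis as the share with LSM ≥ 8.0 kPa.

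**3. Control denominators under the same definition.** The article gives neither the number of controls nor the share f with an LSM. Assume 400 controls with the same prevalences and f from 0 to 20%. Classable controls are 48 × f and 192 × f. The last column is the indicative power to see low-risk referral of 30% in usual care against 10% in the pathway (assumed rates, 192 pathway patients, normal approximation).

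| f | High-risk | Low-risk | Power |
|---|---|---|---|
| 0% | 0 | 0 | none (0/0) |
| 2% | 1 | 4 | 32% |
| 5% | 2 | 10 | 49% |
| 10% | 5 | 19 | 68% |
| 20% | 10 | 38 | 86% |

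The approximation is rough at such small numbers. It also treats the controls with an LSM as a random sample, so it is generous.

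**4. Direction of the selection.** Let r be the true referral rate in a class, and a₁ and a₀ the chances of having an LSM on file if referred and if not referred. The rate seen among controls with an LSM is r·a₁ / [r·a₁ + (1−r)·a₀]. This exceeds r whenever a₁ > a₀, in either class. The bias favours the low-risk half of H3 and works against the high-risk half.

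**5. Overall referral does not test H3.** With 48 high-risk and 192 low-risk patients per 400, and no change among those without NAFLD, the change in overall referral is (48/400)·Δhigh + (192/400)·Δlow = 0.12·Δhigh + 0.48·Δlow. If low-risk referral falls from 30% to 10%, the second term is 0.48 × (−20) = −9.6 points. The total stays unchanged if high-risk referral rises by 9.6/0.12 = 80 points, falls if it rises by less, and rises if by more. H3 is true in all three cases, so the overall proportion cannot identify it.

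**6. Aims 1 and 2.** With identical true disease in both arms, 48/400 = 12% would be detected in the pathway. If fibrosis were recorded only in the 2 to 20% of controls with an LSM, 0.12 × 0.02 = 0.24% to 0.12 × 0.20 = 2.4% would be detected in usual care. With 400 per arm, power for that contrast is above 99.9%. It measures detection, not disease.

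The FibroScan section expects 9 to 15% of examinations to give no valid LSM, which is 36 to 60 of 400 if all are scanned. The outcome text gives no rule for counting a pathway patient who has a prior recorded NAFLD diagnosis but no usable scan. The same record counts as a case in the audit.

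**The case against.** **This is a condensed article.** The mapping of controls to risk groups could sit in the full protocol or analysis plan, and the audit already collects blood tests and simple scores from which a class could be built. That is fair as far as it goes. However, the article itself fixes the class definition, the comparator and the comparator's data, and these conflict as written. A simple-score class would be a different definition from the one stated.

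**Overall referral can be computed.** It can, so it would be wrong to say that Aim 3 yields no comparison at all. What cannot be obtained is the risk-split comparison that H3 states.

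**For Aims 1 and 2, unequal ascertainment is the intervention.** This largely stands. Systematic scanning against what clinicians recorded unaided is a legitimate process contrast. It needs to be labelled as such, with one counting rule for both arms.

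**Stronger readings that the documents do not support:**

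- A reader might infer that selection guarantees the hypothesised result. It does not. The same selection raises high-risk referral in controls, against H3, and no control referral rate is given.
- A reader might turn the historical rate below 5% into a cap of 20 assessed controls per 400. That figure is a detection rate without a stated denominator, and a control who was assessed and found low-risk is not a detected case.
- A reader might infer that alcohol-related steatosis counts as NAFLD only in the pathway. Nothing says usual-care diagnoses exclude drinkers, and alcohol information is sought in both arms.

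**Conclusion.** The concern holds for the risk-split referral comparison and for the cost per appropriate referral. As defined, the control denominators are largely absent, and what remains is probably selected through referral. On the plan's prevalences, 48 high-risk and 192 low-risk pathway patients would face 0 to 10 and 0 to 38 classable controls.

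This rests on three assumptions: 400 controls, equal prevalence in both arms, and 0 to 20% of controls with an LSM on file. That few controls have an LSM is inferred from the audit design and the Discussion's remark on availability; the article gives no share.

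For Aims 1 and 2 the point is narrower. The contrast is valid as documented detection, but it should be named so and counted alike in both arms. The sample-size arithmetic is not at fault.

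**What to change.** 1. Restate the comparative referral outcomes as Hepatology referrals per 100 eligible T2D attendees, within the same fixed window from the index visit in both arms. Split them by the LSM recorded at Hepatology assessment: below 8.0 kPa, 8.0 kPa or above, or not assessed. Base the cost per appropriate referral on the same split.
2. Apply the exclusion for known liver disease under Hepatology follow-up (Exclusion criteria) at the index visit in both arms. If it is applied later, it could remove controls because they were referred.
3. Keep the referral rates with LSM-based denominators as descriptive, pathway-only outcomes.
4. Add FIB-4/NFS strata from routine bloods in both arms as supportive analysis only.
5. For Aims 1 and 2, state that the contrast is documented detection, a process outcome. Count NAFLD documented by any modality in both arms, so that a prior recorded diagnosis with a failed scan is treated as it would be in usual care.

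The cost is a change of wording and a Hepatology record look-up for the referred controls. Some referrals will fall into the unassessed group. The simple scores leave 36 to 63% of patients indeterminate on the Background section's own figure, so they cannot carry the main comparison.

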### Study aims

The primary aims of the study are to determine whether an integrated diagnostic and risk stratification pathway for people with T2D in primary care:

A1: increases the rate of detection of NAFLD and.

A2: increases the number of people identified with advanced fibrosis/cirrhosis.

The secondary aims are to determine whether the pathway:

A3: links people with NAFLD to the “right care” tailored to individual needs (referral of people with increased risk of advanced liver fibrosis to Hepatology clinics) and.

A4: increases the rate of surveillance for HCC among people with a diagnosis of cirrhosis.

We will also evaluate:

A5: the sustainability of the intervention in the current health care system in relation to resource use and costs, and.

A6: the utility of pathway-specific template letters to the General Practitioner (GP) and diabetes specialist that summarise the clinical findings and provide brief recommendations for management and follow-up.

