### Intervention

#### FibroScan

Transient elastography (using FibroScan) has been extensively evaluated; a liver stiffness threshold of 6.5–7.9 kPa has approximately 90% sensitivity in excluding advanced (stage 3–4) fibrosis, whereas LSM > 12–15 kPa is typically present with cirrhosis [31–35]. Transient elastography will be performed by a trained clinician as a point-of-care test, concurrently with the diabetes clinic appointment or when the participant attends for a scheduled blood test, making it easier for participants to have the test performed.

To obtain accurate results from the FibroScan assessment participants will be advised to fast for 3 h before the scheduled time of examination. Clear guidance will be provided to participants regarding fasting and withholding of T2D medications. If the FibroScan appointment is prior to 10 am, participants will be advised to fast overnight and withhold T2D medications until after the examination. If the FibroScan appointment is 10 am or later, participants will be advised to have an early breakfast, and to take their usual T2D medications, and then to fast for 3 h prior to the scan. Participants will be advised to bring a snack and all medications to clinic so that as soon as the FibroScan is completed, they can eat and take their T2D medications as required.

In around 9–15% of examinations, a valid LSM cannot be obtained because a participant’s body habitus or skin to liver capsule depth prevents an accurate assessment [8, 36]. Should this occur, the need for further review of these participants will be determined by the diabetes and study clinicians based on the history, blood tests and imaging available.

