#### Data analysis

Differences in the proportion of patients diagnosed with NAFLD (Aim 1), identified to have advanced fibrosis/cirrhosis (Aim 2), referred to Hepatology (Aim 3), and enrolled in a surveillance program for HCC (Aim 4) before and after implementation of the intervention will be assessed using statistical tests for categorical data (e.g. Pearson’s chi-squared test, McNemar test). Where appropriate we will use regression models to identify associations between variables (eg the association between treatment group (pathway vs. usual care) and clinical and sociodemographic factors).

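### The Aim 4 outcome (HCC surveillance) names three populations and two events, and on its cirrhosis reading it conditions on a diagnosis the pathway is meant to increase

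*Protocol article*

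**What the plan says.** All references are to the Protocol article.

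- **Study aims, A4:** the pathway is to be judged on whether it "increases the rate of surveillance for HCC among people with a diagnosis of cirrhosis". Hypothesis H4 names the same population and sets the contrast against usual care.
- **Secondary outcomes, title:** "Rate of surveillance for HCC among “high-risk” patients".
- **Secondary outcomes, calculation under that title:** the "number of participants with cirrhosis who are referred for surveillance for HCC according to guidelines". No denominator is written out.
- **Design and setting:** "the surveillance for HCC among “high-risk” patients will be compared to patients receiving “usual care" recipients, so again the high-risk group.
- **Data analysis:** the test concerns differences in the proportion of patients "enrolled in a surveillance program for HCC (Aim 4) before and after implementation of the intervention". The same opening phrase also governs Aims 1 to 3.
- **Risk groups (under Other clinical information):** "Participants with LSM ≥8.0 kPa will be classified as" High Risk. The other two groups are no NAFLD and low risk. There is no cirrhosis group.
- **FibroScan:** "LSM > 12–15 kPa is typically present with cirrhosis". This is background and is not used as an outcome definition.

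Three further statements bear on the comparison. Aim A2 is to raise the number of people found to have advanced fibrosis or cirrhosis. The exclusion criteria remove people with known chronic liver disease who are already followed by Hepatology. The usual-care group, a retrospective record audit of the preceding year, has the same exclusions.

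**The concern.** There are two problems.

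The first is definitional. High risk at 8.0 kPa and cirrhosis are not the same group, and being referred for surveillance is not the same event as being enrolled in it. An analysis plan that picks one combination will depart from some other sentence in the protocol.

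The second concerns the comparison that A4 and H4 describe. A rate among people with diagnosed cirrhosis has a denominator that the intervention is designed to enlarge. In the pathway group, the diagnosis follows systematic elastography and then Hepatology work-up. In usual care, it is whatever routine records show, after people under Hepatology follow-up have been removed. The two sets of diagnosed patients need not be alike. A lower rate in the pathway group could therefore sit alongside more people under surveillance, and the result would be hard to interpret in either direction.

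**Working it through.** **Step 1. The plan's own figure.** The document gives no figure for HCC surveillance. Its one interval, in Sample size and statistical power, is for advanced fibrosis: 20% of 240 = 48, with 95% CI 15.4 to 25.5%. The Wilson score interval for 48/240 is 15.43 to 25.52%, so it reproduces and is not in dispute.

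**Step 2. The wordings side by side.**

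| Place | Population | Event |
|---|---|---|
| A4, H4 | diagnosed cirrhosis | surveillance |
| Secondary outcomes, title | high-risk | surveillance |
| Secondary outcomes, calculation | cirrhosis | referred |
| Design and setting | high-risk | surveillance |
| Data analysis | patients (unqualified) | enrolled |

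**Step 3. What the choice of denominator does.** Assumptions: 400 patients; 48 high-risk, borrowing the planning count of advanced fibrosis as a stand-in; *c* of the 48 with cirrhosis; 80% of those with the event. The number of events is 0.8*c*. The rates are 0.8*c*/*c*, 0.8*c*/48 and 0.8*c*/400.

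| *c* (assumed) | Events | Among cirrhosis | Among high-risk | Among all 400 |
|---|---|---|---|---|
| 5 | 4.0 | 80% | 8.3% | 1.0% |
| 10 | 8.0 | 80% | 16.7% | 2.0% |
| 15 | 12.0 | 80% | 25.0% | 3.0% |
| 24 | 19.2 | 80% | 40.0% | 4.8% |

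The ratio of the first rate to the second is 48/*c*, whatever surveillance rate is assumed. Here it runs from 9.6 (*c* = 5) down to 2.0 (*c* = 24).

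**Step 4. What conditioning on the diagnosis can do.** Let usual care diagnose *d0* people and survey a share *s0*, and let the pathway diagnose *d1* and survey *s1*, with groups of equal size. The conditional comparison is *s1* against *s0*. The all-patient comparison is *d1s1* against *d0s0*. They point in opposite directions, against and for the pathway, when *d0*/*d1* < *s1*/*s0* < 1.

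Assume 400 per group (the document gives no size for the usual-care cohort), *d0* = 3, *s0* = 90% and *d1* = 11:

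- With *s1* = 70%, the conditional rates are 90% against 70%. The all-patient rates are 2.7/400 = 0.7% against 7.7/400 = 1.9%.
- The opposite signs persist for any *s1* between 90% × 3/11 = 24.5% and 90%.
- If *s0* is also 70%, the conditional rates are equal, and the all-patient rates are 2.1/400 = 0.5% against 1.9%.
- If *s1* exceeds *s0*, both comparisons favour the pathway.

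Reversal is thus possible over a wide range of *s1*, but it depends on rates that the document does not supply.

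**The case against.** The strongest reply is that the target is clearer than the table suggests. The aim, the hypothesis and the only calculation sentence all say cirrhosis. High-risk appears only in a label and an overview sentence, and a calculation normally governs its label. This stands in part. A reader might infer that two analysts following the text would report rates several-fold apart, but one of them would have to set aside A4, H4 and the calculation. The document does not make that outcome likely.

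Second, the Data analysis sentence can be read as using all patients, since its opening phrase covers Aims 1 and 2, where all patients is the natural meaning. On that reading nothing is conditioned on diagnosis. This also stands. It means the protocol does not firmly commit to an unsound comparison. It does not remove the problem, because that reading disagrees with A4, H4 and the calculation.

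Third, the numbers are soft, and that is right. The 48 is a planning count of advanced fibrosis, not of people at or above 8.0 kPa. The high-risk class applies whatever the steatosis score, so it need not lie within the 240 with NAFLD. The cirrhosis counts and surveillance rates are assumed. A reader might infer that the rate will move against the pathway, or that usual care will have almost no diagnosed cirrhosis. Neither can be derived, and people with known liver disease but no Hepatology follow-up remain eligible.

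Fourth, a reader might infer that the usual-care audit ignores imaging. It does not: Secondary outcomes already lists radiological investigations and liver-clinic referral. What the article does not name is a cirrhosis diagnosis, or whether imaging was for surveillance.

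Last, an all-patient rate mixes detection with uptake. That is a real cost and is dealt with in the fix.

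**Conclusion.** The point holds as an inconsistency in a secondary outcome, with a consequence for interpretation. Population and event differ between sections of the current text, and no section defines cirrhosis for this outcome. On the A4/H4 reading, the between-group rate is not like-for-like: it conditions on a diagnosis that A2 expects the pathway to increase, and the shared exclusion removes the controls most likely to be under surveillance already.

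The rate could therefore move against the pathway while more people are under surveillance. Whether it would, and by how much, cannot be derived from the document; the figures above only illustrate the mechanism under stated assumptions. The primary aims are unaffected.

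**What to change.** 1. Reconcile the aims, hypotheses, design, outcome and analysis sections to one event (referred or enrolled) and one population, and make the outcome title match.
2. Make the between-group comparison for Aim 4 the proportion of all eligible people with type 2 diabetes in each group who have that event. This is compatible with the Data analysis wording.
3. Use the same time window in both groups. Usual care covers 12 months, whereas pathway participants are followed for up to 10 years.
4. Report, descriptively and for each group, the number with diagnosed cirrhosis, the number with the event, and the resulting rate.
5. In the usual-care audit, record cirrhosis diagnosis and mark which of the radiological investigations already collected were for HCC surveillance.

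The cost is rewording, one audit field and one label on an existing field. The drawback is that the all-patient rate will be small and combines detection with uptake, which is why the descriptive rate among diagnosed cirrhosis is kept. Nothing here addresses who should receive surveillance.
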